**Table 3 Tab3:** **Indicators of persistent morbidity**

Indicators of persistent morbidity	Data used to identify	Data source
Use of unscheduled or emergency care for vascular issues	DSS Clinic Identifier and ICD-9 Codes	Outpatient (OPC) files; VA-CMS
Use of scheduled care for polytrauma vascular issues	DSS Clinic Identifier and ICD-9 Codes	OPC files; VA-CMS
Long-term use/escalating dose of opioid medications	VA Product, Dose, Day Supply	Pharmacy Benefits Management (PBM) Data; Medicare Part D VA-CMS
	NDC Code	
Trajectory of chronic pain (latent class analysis of pain scores from TRACC)	Pain Score	CDW vitals
Conditions indicative of persistent morbidity (e.g., Venous stasis disease/venous ulcers, lymphedema)	ICD-9 Codes including but not limited to 729.81, 782.3, 729.5, 415.19, 451.11, 451.19 451.83, 451.82, V72.83	PTF, OPC files, VA-CMS
Prescriptions for compression stockings and wound care supplies (e.g., wound vac) indicative of swelling, venous stasis disease	VA Class	PBM Data, VA-CMS Durable Medical Equipment
	XA	
Use of prosthetic/orthotic devices (canes, walkers, special shoes, etc).	Health Care Financing Administration Coding System (HCPCS) Prosthetic and Sensory Aids Service (PSAS) Code;	National Prosthetics database
		CMS Durable Medical Equipment
Additional procedures (open or endovascular) on the injured extremity	CPT-4; ICD-9A procedure codes	OPC/PTF VA-CMS
Chronic antibody use (osteo or other potential infectious issues with the limb)	VA Product	PBM Data; Medicare Part D VA-CMS
Duplex ultrasound, MRA/CTA or angiogram to evaluate the repair	CPT-4 procedure codes including but not limited to 93970, 93971, 93975, 93976, 93978, 93979, 93922, 93923, 93925, 93926, 93930, 93931, 93924	OPC/PTF; VA-CMS
Mean pain scores over 4	Pain Score Mean per year	Corporate data warehouse Vital Signs
Proportion of VA care	Visits VA/ Total Visits	OPC/PTF; VA CMS outpatient/inpatient
Mortality	Date of Death	VA Vital Status file

### VA medical chart abstraction

We will access the electronic medical record for any VA patient with IILS from the time of VA entry to the time of abstraction, with special attention to functional outcomes including physical therapy, prosthetic care, and care for vascular injuries or conditions such as skin ulcers that may result from graft failure or complications of the initial injury. After development of the electronic data collection template, database, and training, the PI and the chart abstractors will independently review 10 charts and meet together to identify inconsistencies, errors, or disagreements and resolve any by consensus. This will continue until there is 90% agreement on all items abstracted.

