The Military Extremity Trauma Amputation/Limb Salvage (METALS) study applied methods similar to those in the LEAP study to the Operation Enduring Freedom/Operation Iraqi Freedom/Operation New Dawn (OEF/OIF/OND) military population [11]. This retrospective cross-sectional study included 324 U.S. Service members who had sustained major lower limb trauma as a result of high-energy blast and ordnance-related mechanisms. Both unilateral and bilateral lower limb traumatic injuries were included. Clinical data were obtained from participants’ medical records and through telephone interviews. Patients in the limb salvage and amputation groups reported significant disability compared to normal populations and 38% screened positive for depressive symptoms with 34% not working or in school at the time of the interview. Of interest, amputees reported better scores on the SMFA compared to limb reconstruction patients as well as lower rates of post-traumatic stress disorder. Only 17 limb salvage patients (~10%) in the study underwent revascularization [11]. These findings are in contrast to LEAP which reported similar health status measures in amputees and limb salvage patients, suggesting that translation of findings from non-combat civilian settings to combat injury may not be generalizable.

The Late Amputation Study Team (LAST) was to determine the prevalence of late amputations in wounded Service members from OEF/OIF/OND. While most amputations occurred in the acute setting, 15% of Service members sustaining lower extremity injuries had late amputations, defined as greater than 12 weeks after injury, range 12 weeks to 5.5 years [12]. A subset of these patients with type III open diaphyseal tibia fractures managed with late amputation were shown to have an increased incidence of infection [13].

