We will also conduct generalizability analysis using the inverse propensity probability weight technique. [53, 54] The goal is to examine whether the outcome model derived from the VA IILS patients (as described above) can be generalized to the non-VA IILS patients. We first derive model estimates for the VA cohort, then compute the propensity score for receiving non-VA care by modeling the log-odds of receiving non-VA care (vs. VA care) as a linear function of baseline covariates. The inverse propensity weighting is used to calibrate the outcome model derived from the VA IILS patients to the non-VA IILS patients. Finally we assess model generalizability by comparing model estimates between the VA vs. non-VA patients using the diagnostic method by Stuart et al. [55] This generalizability method does not require collecting outcomes for non-VA patients. However the credibility of this method relies on the “ignorability” assumption to hold true: conditioning on the covariates, the counterfactual outcomes of the non-VA patients (the patency outcomes should they receive VA care) would have been the same as the outcomes of the VA patients, and similarly, the counterfactual outcomes of the VA patients (the patency outcomes should they receive non-VA care) would have been the same as the outcomes of the non-VA patients.

Based on preliminary data from the TRACC study, we anticipate that the proportion of OEF/OIF/OND VA patients with ILLS will receive antiplatelet agents/statins/or yearly duplex ultrasound will be no greater than 44.7%. We also assume that the mean vascular repair patency falls between 50%-60%, and that the increased patency due to receiving antiplatelet agents/statins/or yearly duplex ultrasound is no less than 12% (conservatively). Under these conditions, the study will have ≥0.84 power to determine if Vascular Preventive Care processes are associated with positive patient outcomes.

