To address the third aim (Describe patient-reported functional outcomes in Veterans with traumatic vascular limb injuries) we will begin by examining descriptive statistics associated with SMFA, PPFA, CPG scale, SF-8™, and M2C-Q). We will compare scores on these instrument among IILS patients with and without indicators of persistent morbidity, controlling for possible confounders associated with having indicators of persistent morbidity (from Aim 1) including CES-D, and PCL-M. We will then conduct separate generalized estimation equation analyses for each outcome, modeling the mean of each outcome as a linear function of the indicator of having one or more indicators of persistent morbidity and other covariates [52].

Secondary analyses will stratify individuals by initial injury severity type (e.g., vascular only, vascular + orthopaedic, vascular + orthopaedic + nerve, etc.) to further control for initial conditions that may be more difficult to control for in multivariable analyses. We will also examine the role of various prosthetic devices, including the extent to which the technology of the device, the number of different prosthetic devices per limb, etc. mediate the relationship between injury severity, persistent morbidity and functional outcomes. Furthermore, we will conduct generalizability analysis (described above) to examine whether the outcome model derived from the VA patients can be generalized to the non-VA patients.

Our power analysis for the third aim is based on the primary outcome: SMFA. Based on preliminary data, we assume that the proportion of patients with persistent morbidity falls between 10% and 50%. We also assume that the effect size associated with persistent morbidity on SMFA, PPFA, CPG scale, SF-8™, and M2C-Q no less than 0.435. Under those conditions, the study will have >0.80 power to identify a true difference in outcomes among those with and without persistent morbidity.

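### Releasing abstractors on 90% raw agreement over 10 charts does not show that they can detect uncommon late complications

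*Protocol article*

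**What the plan says.** The section on VA medical chart abstraction covers every VA patient with initial in-theatre limb salvage, estimated at about 700 under Study sample. Abstraction is to be done "with special attention to functional outcomes including physical therapy, prosthetic care, and care for vascular injuries or conditions such as skin ulcers". After template development and training, "the PI and the chart abstractors will independently review 10 charts" and then "meet together to identify inconsistencies, errors, or disagreements and resolve any by consensus". The release rule follows: "This will continue until there is 90% agreement on all items abstracted".

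The rule is a plain percentage. Nothing in it refers to events or corrects for chance agreement. It does not say whether the 90% must be met by each item or by all items taken together.

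Three other places bear on the point:
- Study procedures has the DoD and VA data compiled and linked before chart abstraction starts.
- Table 3 takes most indicators of persistent morbidity from coded VA, Medicare, pharmacy and prosthetics files.
- The Background gives one late-event rate, from another cohort: "15% of Service members sustaining lower extremity injuries had late amputations".

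**The concern.** Chart review is most useful for findings that coded data record poorly, such as a skin ulcer that follows graft failure. For an uncommon finding, most charts are negative for every reader. Two readers will then agree on most charts even if one of them cannot recognise the finding. A threshold on overall agreement therefore says little about sensitivity, which is what matters for counting late complications.

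If an abstractor were released with poor detection, the rate of that chart-derived event would be too low, and the data would not show it. Among about 700 charts, an event with 5% to 15% prevalence affects 35 to 105 patients (700 × 0.05 and 700 × 0.15). Partial under-recording would therefore change a descriptive rate noticeably.

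**Working it through.** The 90% is a chosen threshold, so there is no figure to reproduce. The check is how often the rule releases an abstractor who should not be released.

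**Inputs**
- From the article: 10 charts, 90% agreement, and 15% late amputation in another cohort.
- Assumptions: other prevalences (5%, 10%), the number of items on the template, later rounds also of 10 charts, charts that behave like a random draw, a principal investigator who is always right, and comparison of one abstractor with the principal investigator.

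**One item, abstractor never records the event.** Each event chart is a disagreement. Nine of 10 meets 90%, so the item passes if the batch holds at most one event: P(pass) = (1−p)^10 + 10p(1−p)^9.

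| Prevalence p | No event in batch | Exactly one | P(pass) |
|---|---|---|---|
| 5% | 0.599 | 0.315 | 0.914 |
| 10% | 0.349 | 0.387 | 0.736 |
| 15% | 0.197 | 0.347 | 0.544 |

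**One item, abstractor misses half of the events.** At 15% prevalence the disagreement rate per chart is 0.5 × 0.15 = 0.075. P(at most one disagreement) = 0.925^10 + 10 × 0.075 × 0.925^9 = 0.459 + 0.372 = 0.83.

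**Several items, each of which must reach 90%.** For m independent complication items, all missed, P(pass) is the single-item value to the power m. With m = 5:
- 5% prevalence: 0.914^5 = 0.64
- 10% prevalence: 0.736^5 = 0.22
- 15% prevalence: 0.544^5 = 0.05

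A common state behaves differently. The Analytic plan assumes mean patency of 50% to 60%, so non-patency is 40% to 50%. If it were abstracted as an item, an abstractor who never recorded it would pass with probability 0.046 at 40% and 0.011 at 50%.

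**Items pooled.** With K items there are 10K cells, and K disagreements are allowed. If m of the items are complications, all missed, the misses follow Bin(10m, p). At 15% prevalence:
- 5 of 20 items: about 7.5 misses expected, 20 allowed, P(pass) about 1.00
- 10 of 30 items: about 15 expected, 30 allowed, P(pass) about 1.00
- 10 of 20 items: about 15 expected, 20 allowed, P(pass) 0.93
- 20 of 20 items: about 30 expected, 20 allowed, P(pass) 0.03

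So pooled agreement releases this abstractor almost always at prevalences up to 15%, provided that complications make up no more than about a third of the template.

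**The case against.** A reader might infer that the rule would release an abstractor who misses every late complication, and that the study's complication and morbidity rates are therefore unreliable. The article does not support that, for four reasons.

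- **The 54% and 91% are for one item.** If each item must reach 90%, missing five complications at 15% prevalence passes only about 5% of the time, and missing a common state is nearly always caught. The stronger reading needs pooled agreement, which the article neither states nor excludes.
- **There is a safeguard in the same section.** The principal investigator reads the same charts, and every disagreement is discussed even when 90% is reached. An event that the principal investigator sees therefore reaches the meeting. It can do so only if the batch contains an event, and 20% of batches at 15% prevalence and 60% at 5% contain none. The meeting may teach the abstractor, but a single miss still does not block release.
- **Most morbidity indicators are not abstracted.** Table 3 takes venous ulcers, further procedures, emergency care, imaging use, drugs, devices and mortality from coded or administrative files. The first aim uses merged VA, Medicare and DoD study data. Abstractor error would not misclassify those indicators.
- **The benchmark is borrowed.** The 15% comes from a different cohort. Late amputation is also hard to overlook in a chart, so it serves as a prevalence and not as a likely miss.

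A reader might also infer that the calibration charts are unselected and that agreement is never checked again. The article is silent on both. The full protocol or abstraction manual may cover them, so neither is a finding.

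What remains is that the stated release criterion does not itself test detection of uncommon events, and that its unit is ambiguous.

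**Conclusion.** The point holds in a limited form. For one uncommon chart-derived item, the stated rule passes an abstractor with no sensitivity in 54% of batches at 15% prevalence and 91% at 5%, and one with half sensitivity in 83% at 15%. Read as pooled agreement, it hardly constrains detection of complications. Read item by item, it usually catches an abstractor who misses several complications at 10% to 15% prevalence, but not reliably at 5% (64% pass with five items).

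These figures rest on assumed prevalences and item counts, independence between items and randomly drawn charts, none of which the article gives. They describe the threshold alone, before any learning at the consensus meeting. The effect is confined to items taken from the chart, and no power or sample-size figure depends on the rule. This is an inexpensive improvement to a stated procedure and does not threaten the study's main analyses.

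**What to change.** In the section on VA medical chart abstraction:

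1. State that the 90% applies to each item.
2. Use the already linked ICD-9 and CPT data to choose calibration charts so that about half carry a late complication. Add some unflagged charts, because training only on coded events would not test the uncoded ones, where chart review adds most.
3. For the key event items, also require at least 90% agreement on charts that are positive by consensus. Accumulate these over rounds so that each event type has several positives.

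The third step does most of the work. With five positives, 90% means five of five: an abstractor with no sensitivity never passes, and one who misses half passes with probability 0.5^5 = 0.03. With ten accumulated positives, one miss is allowed: the abstractor who misses half passes with probability 11/1024 = 0.01, while one with 95% sensitivity passes with probability 0.599 + 0.315 = 0.91.

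The cost is possibly one or two more training rounds with the same staff. Outcomes, sample size and the abstraction template need not change.

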### Survey data

After obtaining the appropriate IRB approvals, HIPAA, and OMB waivers we will proceed with the interview and survey component using a modification of the Dillman method [40]. During the chart abstraction process, we will obtain the contact address for individuals in the cohort and send a pre-notification letter, which will include a study information sheet, directions on how to access the survey online, and a toll-free telephone number to call to opt out of the survey. Two weeks later we will call individuals who have not opted out. Research staff will first obtain verbal consent from the Veteran to proceed and then will conduct the initial interview that addresses the Veteran’s understanding of their injury, vascular repair, and medical care since the original injury. The research staff will then answer questions regarding completion of the outcomes survey, which will be offered online or by mail/telephone options. If the Veteran requests a mailed survey, the research team will promptly send a packet containing the survey, and a stamped envelope for the participant to return the survey. If the individual requests telephone survey, research staff will offer the Veteran the opportunity to complete the survey at that time or to schedule a time convenient for the Veteran.

For the online/mail survey, one week after the interview, the research team will send a letter thanking those who have responded and remind non-respondents to reply, followed 2 weeks later by a second mailed invitation to non-respondents to complete the on-line survey (or mailed back-up). We will provide a gift card to participants who complete the mailed surveys.

The primary survey outcome measure for this study is one used for the GWOT VI: the *Short Musculoskeletal Function Assessment*. Additional instruments include the Paffenbarger Physical Activity Questionnaire, Chronic Pain Grade Scale, and the Military to Civilian Questionnaire MC2-Q (a measure of community re-integration). *Short Musculoskeletal Function Assessment* (SMFA) is a validated, 46-item self-reported health status questionnaire on extremity functional status. The SMFA contains two parts: the dysfunction index and the quality-of-life limitation index. The SMFA questionnaire has excellent internal consistency and stability, with most values greater than 0.90. Content validity for the dysfunction and bother indexes was supported with few ceiling effects (less than 5 percent), and no floor effects. Moreover, significant correlations were found between the SMFA dysfunction and other indexes and the physicians’ ratings of patient function (*e.g*., recreational and leisure activities, activities of daily living, and emotional function [rho ≥ 0.40]) and clinical measures including grip strength and walking speed [rho ≥ 0.40] [41].

*The Paffenbarger Physical Activity Questionnaire*
[42] (PPAQ) is a validated scale that describes participation in physical activity more specific to sports and leisure which has been used in a number of prior studies including the METALS study [11]. This instrument asks respondents to identify up to 4 activities performed in the past three months, the amount of time spent in those activities, and the intensity of those activities. This instrument allows a calculation of the approximate metabolic equivalents (METS) expended (e.g. an adult sitting quietly expends 1 MET). We will use Ainsworth’s Compendium of Physical Activities [43] to classify reported activity by the rate of expended energy into METS in the same manner used by the METALS study to improve comparability to findings.

*The Chronic Pain Grade (CPG) scale*
[44] is a validated measure of the severity of chronic pain. Similar to the METALS study, we will use the pain interference questions to distinguish the extent to which physical function and activities of daily living are affected by the pain [11].

*The SF-8™* is the first SF survey to be constructed on the basis of empirical studies linking each questionnaire item to a comprehensive “pool” of widely used questionnaire items, including but not limited to the SF-36®, proven to measure the same health concepts. Because the item “pool” for each of the eight health concepts was calibrated on the same metric as the corresponding SF-36® Health Survey scale, each SF-8™ single-item scale and the SF-8™ summary measures can be scored on the same norm-based metrics as the SF-36® scales and summary measures. Thus, the SF-8™ is an 8-item version of the SF-36® that yields a comparable 8-dimension health profile and comparable estimates of summary scores for the physical and mental components of health [45]. Therefore, we will use the SF-8™ rather than the SF-36™.

The Military to Civilian Questionnaire is a validated, 16 item self-reported measure of experiences during military to civilian transition, developed by Sayer and colleagues at the Minneapolis VA/Polytrauma Center [46]. It was validated using a, stratified sample of 1,226 Iraq and Afghanistan Veterans who used VA medical care. The internal consistency of the M2C-Q was .95 in this sample. Factor analyses indicated a single total score was the best-fitting model. Total scores were associated with measures theoretically related to reintegration difficulties including perception of overall difficulty readjusting back into civilian life (R^2^ = .49), probable PTSD, probable problem drug or alcohol use, and overall mental health. Subgroup analyses revealed a similar pattern of findings in those who screened negative for PTSD.

In addition to these outcome variables, we will collect self-reported behavioral health symptoms.

Depression Severity will be assessed with the Center for Epidemiologic Studies Short Depression Scale (CES-D 10), which has been demonstrated to be a valid and reliable measure to assess depression in both VA and non-VA settings [47–49]. The 10 items are rated on a 0 (rarely or none of the time) to 3 (all of the time) scale. Items for this instrument have not been directly mapped onto the 9 DSM IV diagnostic criteria for Major Depression, but the sensitivity and specificity average 80% and 70% respectively with regard to results from a formal diagnostic interview [47, 48]. PTSD Severity will be assessed with the PTSD Checklist-Military (PCL-M) [50]. The PTSD Checklist is a 17-item self-report measure designed to assess the diagnostic criteria of re-experiencing, avoidance and numbing, and hyperarousal. Respondents indicate on a 5-point scale (“Not at all” to “A great deal”) how much they were bothered by each symptom in the past month.

### Other data for spatial analysis

Research staff will contact vascular surgery, surgery, and physical medicine and rehabilitation clinics at each VA hospital to determine the extent to which VA facilities use contracts for vascular surgery patients and will identify sites with external contracts for vascular surgery, rehabilitation medicine and prosthetics care to create a data set to be used in our spatial analysis.

### Analytic plan

To address the first aim, we will compare injury, demographic and geospatial characteristics of patients IILS and identify late vascular surgery related limb complications and health care utilization in Veterans receiving VA vs. non-VA care using merged VA + VA-Medicare and DoD study data. We will identify vascular procedures performed, limb salvage survival time, and indicators of persistent morbidity over time (*e.g*., frequent/emergency care for vascular-related conditions, venous stasis disease, prosthetic use, long-term opioid therapy [VA patients only]). We will calculate descriptive statistics for all IILS patients’ demographic characteristics, long-term clinical outcomes (surgery related limb complications, time to amputation, persistent morbidity), and healthcare utilization (note that long-term use of opioid therapy will be assessed only among VA patients). We will also compare these descriptive statistics between those who received VA vs. non-VA care using chi-square tests for categorical variables and t-tests for continuous variables (with appropriate Box-Cox power transformation if necessary).

To address the second aim, characterize the preventive services received by individuals with vascular repair and related outcomes, we will first compute the proportion of patients who receive antiplatelet agents, statins, annual duplex ultrasound, and vascular specialty care (and categories described above), and the percent patency each year for individuals without amputation. We will then examine the relationship between percent patency and preventive care using random effects analyses that models the vascular repair patency as a linear function of the indicator of receiving antiplatelet agents, statins, duplex ultrasound [51, 52], and other covariates/confounders (e.g., number of limbs affected, any initial, early or late amputations, mental health comorbidity, TBI diagnosis, and pre-existing chronic disease states such as atherosclerosis, diabetes, peptic ulcer disease), where the random effect is used to adjust for the within facility correlation, and the inverse of the propensity score for receiving antiplatelet agents/statins/yearly duplex ultrasound is adjusted for as weights. The adjustment of the propensity score for receiving antiplatelet agents/statins/yearly duplex ultrasound will minimize the estimation biases due to confounding by indication. We will also create different cut points (e.g. 75%, 50% patent), and use a binary outcome model. If Vascular Preventive Care processes are associated with positive patient outcomes, there will be support for these care processes as best practices.

We will also conduct generalizability analysis using the inverse propensity probability weight technique. [53, 54] The goal is to examine whether the outcome model derived from the VA IILS patients (as described above) can be generalized to the non-VA IILS patients. We first derive model estimates for the VA cohort, then compute the propensity score for receiving non-VA care by modeling the log-odds of receiving non-VA care (vs. VA care) as a linear function of baseline covariates. The inverse propensity weighting is used to calibrate the outcome model derived from the VA IILS patients to the non-VA IILS patients. Finally we assess model generalizability by comparing model estimates between the VA vs. non-VA patients using the diagnostic method by Stuart et al. [55] This generalizability method does not require collecting outcomes for non-VA patients. However the credibility of this method relies on the “ignorability” assumption to hold true: conditioning on the covariates, the counterfactual outcomes of the non-VA patients (the patency outcomes should they receive VA care) would have been the same as the outcomes of the VA patients, and similarly, the counterfactual outcomes of the VA patients (the patency outcomes should they receive non-VA care) would have been the same as the outcomes of the non-VA patients.

Based on preliminary data from the TRACC study, we anticipate that the proportion of OEF/OIF/OND VA patients with ILLS will receive antiplatelet agents/statins/or yearly duplex ultrasound will be no greater than 44.7%. We also assume that the mean vascular repair patency falls between 50%-60%, and that the increased patency due to receiving antiplatelet agents/statins/or yearly duplex ultrasound is no less than 12% (conservatively). Under these conditions, the study will have ≥0.84 power to determine if Vascular Preventive Care processes are associated with positive patient outcomes.

To address the third aim (Describe patient-reported functional outcomes in Veterans with traumatic vascular limb injuries) we will begin by examining descriptive statistics associated with SMFA, PPFA, CPG scale, SF-8™, and M2C-Q). We will compare scores on these instrument among IILS patients with and without indicators of persistent morbidity, controlling for possible confounders associated with having indicators of persistent morbidity (from Aim 1) including CES-D, and PCL-M. We will then conduct separate generalized estimation equation analyses for each outcome, modeling the mean of each outcome as a linear function of the indicator of having one or more indicators of persistent morbidity and other covariates [52].

Secondary analyses will stratify individuals by initial injury severity type (e.g., vascular only, vascular + orthopaedic, vascular + orthopaedic + nerve, etc.) to further control for initial conditions that may be more difficult to control for in multivariable analyses. We will also examine the role of various prosthetic devices, including the extent to which the technology of the device, the number of different prosthetic devices per limb, etc. mediate the relationship between injury severity, persistent morbidity and functional outcomes. Furthermore, we will conduct generalizability analysis (described above) to examine whether the outcome model derived from the VA patients can be generalized to the non-VA patients.

Our power analysis for the third aim is based on the primary outcome: SMFA. Based on preliminary data, we assume that the proportion of patients with persistent morbidity falls between 10% and 50%. We also assume that the effect size associated with persistent morbidity on SMFA, PPFA, CPG scale, SF-8™, and M2C-Q no less than 0.435. Under those conditions, the study will have >0.80 power to identify a true difference in outcomes among those with and without persistent morbidity.

